# Association Between Refrigerator Openings and Protein Intake After Hospitalization for Heart Failure Decompensation: Protocol for a Prospective Cohort Pilot Study

**DOI:** 10.2196/66299

**Published:** 2025-08-18

**Keywords:** ambient sensor system, digital health, older people, muscle mass, muscle strength, nutrition assessment, protein intake

## Abstract

**Background:**

Sarcopenia, characterized by loss of muscle mass, reduced strength, and increasing frailty, is common in older adults and is often the result of underlying diseases such as advanced stages of heart failure (HF). Protein intake is crucial for maintaining muscle mass and strength. However, older adults typically consume less protein compared to younger individuals. It has recently been shown that the time of the first refrigerator opening in the morning, indicated by a door sensor, may be correlated with frailty in older individuals living alone.

**Objective:**

The aim of this study is to determine whether the time of the first refrigerator opening in the morning can serve as a potential indicator of protein intake in older patients (age ≥70 years) after hospitalization for HF decompensation over a period of 6 months.

**Methods:**

This is a substudy of a prospective interventional cohort study that aims to identify changes in digital biomarkers derived from an ambient sensor system, which may support the early detection of HF decompensation. In this substudy, the frequency and timing of refrigerator door openings in participants’ homes will be measured. To assess associations between protein intake and refrigerator openings, dietary intake will be evaluated using 24-hour dietary recalls at 3 different timepoints: at 1, 3, and 6 months after hospital discharge. All 24-hour dietary recalls will be conducted by trained dietitians in face-to-face interviews on weekdays. The primary outcome of this study will be the correlation between protein intake and the time (in minutes after midnight) of the first refrigerator door opening at each of the 3 assessment points.

**Results:**

The study is currently in the data collection phase. Recruitment began in February 2024. Data analysis will begin after all data have been collected. As of manuscript submission, 12 patients have been recruited. Results are expected to be published by the end of 2025.

**Conclusions:**

Considering that protein-rich foods are typically stored in the refrigerator, the relationship between frailty and refrigerator usage may be a relevant indicator for nutritional assessment, particularly regarding protein intake. In addition, sarcopenia and frailty may also be linked to protein distribution across meals. This study will explore whether monitoring refrigerator openings can serve as a simple method for identifying increased risk of frailty and sarcopenia. Early detection through such monitoring could facilitate timely interventions and potentially reduce the risk of these conditions.

**Trial Registration:**

ClinicalTrials.gov NCT06126848; https://clinicaltrials.gov/study/NCT06126848

**International Registered Report Identifier (IRRID):**

DERR1-10.2196/66299

## Introduction

The population of older people is increasing significantly around the world, including in Switzerland [1]. With higher life expectancy and increasing age, the risk of diseases characterized by a decline in muscle mass is also rising [2,3]. Loss of muscle mass and strength is associated with an increased risk of mobility impairment, fractures, prolonged hospitalization, hospital readmission, reduced quality of life, morbidity, and mortality [2,4-6]. These conditions arise due to a combination of reduced food intake, increased nutrient requirements, metabolic changes, sepsis, trauma, aging, and physical inactivity [4]. The interplay between malnutrition, sarcopenia, and frailty in older people has already been demonstrated in many studies [7-10]. A systematic review and meta-analysis has shown that about half of hospitalized older adults suffer from 2 or even 3 of these diseases or precursors [3].

Furthermore, sarcopenia and frailty are often the result of other underlying diseases such as chronic heart failure (HF). The prevalence of sarcopenia has been found to be 55% (95% CI 43-66) in hospitalized patients with HF and 26% (95% CI 16-37) in nonhospitalized patients [11]. Additionally, 79% of patients with HF are frail. This, in turn, may be associated with reduced quality of life and poor prognosis [12]. Overall, diet quality is associated with the risk of frailty, and poor intake is adversely related to muscle mass and strength [13,14]. Nutritional status is, therefore, also a crucial risk factor for the development and prognosis of HF.

Due to the high prevalence of sarcopenia and frailty in patients with HF, more attention should be paid to protein intake as an important influencing nutritional factor [14-16]. To achieve this, the protein intake of patients with HF in the home environment must first be assessed. Ideally, simple, valid instruments should be used for this purpose. Common screening tools such as the Mini Nutritional Assessment (MNA) are insufficient to recognize people with low energy and protein intakes [17]. Currently, a number of screening and assessment tools are available [18]; however, the assessments with these tools are very time-consuming for long-term monitoring at home and therefore not very feasible for application in HF patients’ everyday lives.

Digitalization can offer new possibilities that allow patients with HF living at home to be monitored easily and regularly. It has been shown that a sensor system using interaction-free, contactless, and inexpensive sensors is suitable for long-term monitoring of physical activity, sleep, and door openings, including the refrigerator door in the homes of older people living alone [19]. Considering that protein-rich foods (such as meat, meat products, fish, milk, and dairy products) are typically stored in the refrigerator, the relationship between frailty and use of the refrigerator door could be an important indicator for nutritional status in terms of protein intake. Furthermore, sarcopenia and resulting frailty may also be linked to protein distribution across meals. To date, very few studies have investigated this. A study among older women in the Nurses’ Health Study indicates that consuming at least 30 g of protein over 2 or more meals could be more effective for maintaining muscle mass and physical performance compared with eating a single high-protein meal [20]. In addition, 2 recent studies in older populations indicate that skipping breakfast increases the risk of frailty [21,22]. A Japanese survey (n=2468) showed a correlation between breakfast habits and frailty in older people aged 75 and over. Breakfast skippers generally had lower food intake and poorer nutrient density than daily breakfast consumers. The multivariable-adjusted odds ratio (95% CI) of breakfast skippers for frailty was 1.62 (1.04-2.52; *P*=.032) in one model (adjusted for age, sex, body mass index, and living alone) [22].

The use of refrigerator openings (eg, the first door opening of the day or frequency) as indicators for increased risk of sarcopenia and frailty would provide an easy monitoring opportunity. In this context, the study by Schütz et al has shown that the time of the first refrigerator opening in the morning indicated by a door sensor at the refrigerator may correlate with frailty in older single living persons [19]. Notably, approximately one-third of older people in Switzerland live alone [23], emphasizing the relevance of such monitoring approaches. Prior studies have also shown that living alone increases the odds of falling among community-dwelling older adults [24-26]. With such simple assessment tools, interventions could be initiated at an early stage to reduce the risk of these diseases. This, in turn, would have a positive impact on the quality of life of those affected and could also help to reduce health care costs.

As a part of prospective interventional cohort study (for details refer to study protocol of Vögeli et al [27]), a substudy will be conducted with the aim of evaluating the sensitivity and specificity of the time of the first refrigerator opening in the morning as a potential indicator for protein intake in older patients after hospitalization for HF decompensation over a period of 6 months.

## Methods

### Study Design and Participants

In this prospective cohort pilot study, 24 consecutive patients living alone at their homes who were hospitalized for HF decompensation at 2 secondary care hospitals (Solothurner Spitäler AG) in Olten and Solothurn, Switzerland, will be included.

The inclusion criteria are current hospitalization for HF decompensation, age≥70 years, left ventricular ejection fraction <50% and treatment with diuretics, New York Heart Association class II or III, living alone, willingness to participate with informed consent, and agreement to attend follow-up visits at the hospital at 3 and 6 months. Exclusion criteria include major depression (9-item Patient Health Questionnaire [PHQ-9] score >9) or being on hemodialysis. In addition, patients with a left ventricular assist device, or those who had undergone coronary revascularization or cardiac resynchronization therapy implantation within 28 days before the index event of HF decompensation, or have been scheduled for such interventions, are excluded from the study.

### Assessment

#### Baseline Assessment

The baseline parameters that will be evaluated at hospital entry have been previously described [27].

#### Dietary Assessment

For dietary assessment, food intake will be measured using the 24-hour dietary recall. The 24-hour dietary recall is an open-ended, retrospective dietary assessment method. It aims to record as much detailed information as possible about all foods and drinks consumed by the respondent in the previous 24 hours or the day before [28]. In this study, 24-hour dietary recalls are conducted at 3 different timepoints, at 1 month (optional), 3, and 6 months after hospital discharge. The first 24-hour dietary recall at 1 month is optional, as—unlike the assessments at 3 and 6 months—it cannot be coordinated with a routine follow-up hospital visit. Conducting this assessment would require an additional clinic or home visit, which was deemed burdensome for participants. To reduce participant burden and support adherence, this timepoint was made optional. All 24-hour dietary recalls will be conducted on weekdays by trained dietitians in face-to-face interviews. As the main drawback of this method is the forgetfulness of the participants, the 24-hour dietary recalls will be conducted by using the Automated Multiple-Pass Method (AMPM), as described elsewhere [29]. The AMPM uses multiple memory cues with standardized wording to elicit recall of all possible foods. Before the start of the 24-hour dietary recall, it will be recorded whether the day surveyed reflected a usual day in terms of diet or whether it was an unusual day. A usual day is defined as a day on which the participant ate according to their usual habits and routines, reflecting habitual dietary intake. This terminology was chosen to emphasize the importance of capturing habitual intake patterns. Conversely, an unusual day is determined based on the participant’s own judgment and refers to any day they perceive as not representative of their usual intake. Examples will be provided to participants, for example, holidays, celebrations, excursions, acute illness, or other events that may have significantly altered their eating behavior. The amount of consumed food will be estimated using the photo book of the National Nutrition Survey in Switzerland (menuCH) [30] (Multimedia Appendix 1). The conversion of the estimated amounts into weights will follow the menuCH photo book manuals and commercially available packaging sizes in Switzerland. All conversions will be performed by experienced dietitians. Protein intake in grams (g) and energy intake in kilocalories (kcal) will be calculated using nut.s nutritional software (version 1.33.10 - 2022.08.26; dato Denkwerkzeuge) based on the 24-hour dietary recalls. The nutritional database used in nut.s is adapted for the evaluation of Swiss food products.

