#### Refrigerator Door Sensors

The refrigerator at the patient’s home will be equipped with a door sensor recording the opening and closing events of the fridge door. This sensor consists of a small magnet fixed on the door and a sensor with a reed relay attached to the frame. When the door opens or closes, the sensor immediately sends this information to a base unit through an encrypted radio frequency protocol continuously with a resolution of 1 second. The base unit collects the data and sends it to the cloud in real time using the Global System of Mobile Communication networks. The duration of each refrigerator opening is calculated as the time difference between the opening and closing events. The system has been described in detail in the main study, where the sensor system is used to collect digital markers beyond refrigerator openings with the aim of evaluating the system’s potential to detect HF decompensation [27]. The integration of the magnetic refrigerator door sensor into the sensor system to detect refrigerator openings represents a minor extension to the overall setup. The high reliability of the ambient sensor system, with extremely low susceptibility of the sensor and the transmission system, has been shown previously [27]. The refrigerator door sensors will be installed at the patient’s home within 1 week after hospital discharge. Frequency and timing of refrigerator openings are collected over a 6-month period after hospital discharge. The assessment during the study is shown in Figure 1.

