### Statistical Analysis

We will compute the cross-sectional correlations between protein intake (g) and first refrigerator door opening after midnight in minutes (RDmin) at the start (1 month) and at 3 and 6 months (primary outcome). Further, quantities of interest are the correlation between protein intake (g) and refrigerator opening frequency per day (RDfreq), between energy intake (kcal) and RDmin and RDfreq, between (risk of) malnutrition (score) and RDmin and RDfreq, and between HGS (kg) and RDmin and RDfreq. From the time series of refrigerator opening time after midnight in minutes over the period of 6 months, we will create 3 time windows, each window representing the 2-week period prior to each nutrition assessment (Figure 1). For each window, a mean RDmin measurement will be calculated, resulting in 3 RDmin measurements, 3 RDfreq, and 3 measurements of protein intake (g) and energy intake (kcal) from the 24-hour dietary recalls, 3 measurements of malnutrition and HGS (after 1, 3, and 6 months). We will estimate the cross-sectional associations between RDmin and RDfreq and protein intake (g), energy intake (kcal), (risk of) malnutrition (score), and HGS (kg) at 1, 3, and 6 months to quantify the correlation and to assess the stability of this correlation over time. We will compute Spearman correlation coefficients with corresponding 95% CIs.

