### Limitations

This study has several limitations. First, the patterns of refrigerator openings—regarding time of day and frequency—may be subject to great variations, and the use of single values or combinations of values will require both internal and external validation. Second, the study is limited to patients who live alone. This complicates the generalizability of the results to other populations with HF. The small sample size is based on experience from a previous study, including a similar patient population with hospitalization for HF decompensation. At present, no prior data are available to support a formal power calculation. Third, to verify the accuracy of the refrigerator openings in assessing the protein intake, results must be compared with a standard reference method. This is done in this study with a 24-hour recall. As a retrospective method, it also has weaknesses, in particular, recall bias or unusual eating days. For this reason, at least two 24-hour dietary recalls per person are carried out.

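### The 1-month correlation is one of three primary correlations, but the 1-month recall is optional, so that coefficient and the stability comparison rest on whichever patients accept an extra visit

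*Protocol article*

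**What the plan says.** The Abstract (Methods) defines the primary outcome as the correlation of protein intake with the "time (in minutes after midnight) of the first refrigerator door opening at each of the 3 assessment points". Statistical Analysis repeats this, placing the cross-sectional correlations "at the start (1 month) and at 3 and 6 months (primary outcome"). It then describes the data as "resulting in 3 RDmin measurements, 3 RDfreq, and 3 measurements of protein intake (g"), with energy intake, malnutrition score and handgrip strength also at three times, and plans to use the three coefficients to judge whether the correlation is stable.

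Other sections give the 1-month assessment a different status. Under Dietary Assessment, "The first 24-hour dietary recall at 1 month is optional". The reason is that it cannot be joined to a routine hospital visit: "Conducting this assessment would require an additional clinic or home visit, which was deemed burdensome for participants". The sections on anthropometry, MNA-SF and handgrip strength each mark their own 1-month measurement as optional too. Study Design and Participants requires only "agreement to attend follow-up visits at the hospital at 3 and 6 months". Limitations promises that "at least two 24-hour dietary recalls per person are carried out", that is, two and not three.

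The door sensor is not optional in this way: "Frequency and timing of refrigerator openings are collected over a 6-month period after hospital discharge", with installation within a week of discharge.

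**The concern.** A primary time point should be one that the design intends to observe in everyone. Here the article itself fixes both the primary status and the optional status of the 1-month recall, and Statistical Analysis does not acknowledge the optional status.

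Three things are at stake.

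- **Precision.** Every patient who declines is lost from one primary coefficient, in a cohort planned at only 24.
- **Bias.** The patients are aged 70 or over, live alone and have recently been discharged after decompensation. Taking on an extra assessment may go with being less frail. The article's own rationale links frailty both to the time of first opening and to diet. A trait related to uptake and to both analysed variables can shift a correlation computed only in those who accept.
- **Stability.** If the 1-month set is a subset and the later sets are fuller, a difference between the coefficients may reflect who was measured and not when.

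**Working it through.** **The document has no figure to reproduce.** It gives no power calculation, target correlation or expected uptake. What follows illustrates size under stated assumptions.

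**Step 1: status of each time point.**

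| Time point | Primary correlation? | Recall secured by the design? |
|---|---|---|
| 1 month | Yes (Abstract; Statistical Analysis) | No: optional (Dietary Assessment) |
| 3 months | Yes | Yes: agreement to the visit is an inclusion criterion |
| 6 months | Yes | Yes: same |

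The secured recalls number two, which agrees with Limitations and not with the three counted in Statistical Analysis.

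**Step 2: precision.** Inputs: n = 24 (Study Design and Participants); an assumed observed correlation r = -0.4; an assumed uptake of 50%, so n = 12. The approximate 95% CI is tanh(atanh(r) ± 1.96 × SE), with SE = 1/√(n - 3) and atanh(-0.4) = -0.424.

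- n = 24: SE = 1/√21 = 0.218. Limits on the z scale are -0.424 ± 0.428, giving -0.69 to 0.00.
- n = 12: SE = 1/√9 = 0.333. Limits on the z scale are -0.424 ± 0.653, giving -0.79 to 0.23.

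That SE is the one for a Pearson coefficient, whereas the plan uses Spearman. With the Spearman-adjusted SE = √((1 + r²/2)/(n - 3)) = √(1.08/(n - 3)), the SEs are 0.227 and 0.346. The intervals become -0.70 to 0.02 and -0.80 to 0.25, so the conclusion is the same.

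**Step 3: possible bias.** Assumptions: a fitness trait correlates a with protein intake and -a with RDmin; the Pearson correlation in all patients is -0.40, which corresponds to a Spearman value of (6/π) × arcsin(-0.40/2) = -0.385; and 50% accept. Graded selection means that the probability of accepting rises with fitness on a logistic curve with slope 1.5. Sharp selection means that only the fitter half accept. By simulation, the Spearman value in those who accept is:

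| a | Graded selection | Shift | Sharp selection | Shift |
|---|---|---|---|---|
| 0 (uptake unrelated) | -0.38 | none | -0.38 | none |
| 0.3 | -0.37 | 0.02 | -0.35 | 0.04 |
| 0.5 | -0.34 | 0.05 | -0.27 | 0.11 |
| 0.7 | -0.29 | 0.10 | -0.11 | 0.27 |

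Under graded selection, uptake of 75% or 33% in place of 50% keeps the shift between about 0.01 and 0.05 for a = 0.3 to 0.5.

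**Step 4: is a = 0.7 credible?** It implies a partial correlation of protein and RDmin, given fitness, of (-0.40 + 0.7²)/(1 - 0.7²) = 0.09/0.51 = +0.18. Among equally fit patients, later opening would then go with higher protein intake. A single-day recall would also have to correlate 0.7 with fitness. That is an extreme case, and no weight is placed on it.

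**Step 5: can patients without the recall be compared with those who have it?** Yes, in several ways. Baseline parameters are recorded, and intake, MNA-SF, weight and handgrip strength are measured at 3 and 6 months. Sensor data exist as well. Taking a month as 30 days, a two-week window before 1 month covers about days 16 to 30, after installation by day 7. One detail is needed: the plan ties each window to a nutrition assessment, and a patient who declines has no such date at 1 month, so a nominal date must be set.

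**The case against.** The strongest reply has four parts.

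1. **The document does not say that frail patients decline.** A reader might infer that burden is why individuals refuse, so that the 1-month coefficient describes only the fitter patients. The text does not support this. Burden is the investigators' reason for making the assessment optional, no reasons for refusal are recorded, and a home visit is possible, so a patient who cannot travel is not shut out. This stands: selection related to frailty is a possibility, not a stated fact.
2. **The likely bias is small.** A reader might also infer heavy attenuation, for example to -0.11. That needs the extreme assumption shown in the working. Under moderate graded selection, a shift of 0.02 to 0.05 is small beside an interval at n = 24 whose half-width is about 0.35. This stands as well.
3. **Reporting details belong elsewhere.** The number contributing at each time point and the handling of missing recalls are commonly left to a full protocol or SAP, so their absence from the article is no fault, and it does not follow that readers could never see the selection. This is accepted. It does not reach the conflict itself, because the article fixes both the primary status and the optional status.
4. **This is a pilot with separate cross-sectional coefficients.** Selection at 1 month cannot affect the coefficients at 3 and 6 months. That is correct for the coefficients. It does not protect the comparison between time points, and a small sample makes the loss of patients more costly.

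**Conclusion.** The point holds in a limited form. The article names as primary a correlation whose data it does not secure, and it counts three protein measurements where the design secures two. The loss of precision follows directly if patients decline: with half declining and r = -0.4, the upper confidence limit moves from about 0.00 to about 0.23. Bias is conditional. It is absent if uptake is unrelated to frailty and diet, and about 0.02 to 0.05 under the moderate graded selection assumed here. The planned judgement of stability is exposed to a change in the set of patients whenever the 1-month set is incomplete. Uptake, the true correlation and the strength of selection are all assumptions, and the documents give none of them. The 3- and 6-month coefficients are unaffected. The matter should be settled before analysis but does not undermine the study.

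**What to change.** - **Primary outcome.** In the Abstract and in Statistical Analysis, define it as the protein–RDmin correlations at 3 and 6 months. Report the 1-month correlation as secondary or exploratory, with the number of patients contributing. Correct the count of three measurements to say that the first is optional.
- **Stability.** Make any comparison involving 1 month only in patients with all three recalls.
- **Selection check.** Compare patients with and without the 1-month recall on baseline parameters, on their 3- and 6-month values, and on RDmin and RDfreq. For patients without the recall, use a two-week sensor window before a nominal 1-month date fixed in advance.

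**Cost.** No new visits or data are needed. It is, however, more than rewording: it is a change to the primary outcome of a registered study with 12 of 24 patients recruited as of June 2025, so it should be dated and justified. The article says that analysis starts only after all data are collected, so the change can precede it. The study would have two primary time points instead of three, and the comparison restricted to patients with all three recalls would have fewer patients.
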